## Methods and analysis

### Study design and setting

BARI-LIFESTYLE observational study is a prospective, longitudinal cohort study within routine clinical care setting of patients undergoing bariatric surgery conducted in London, UK (figure 1). A total of 100 patients who are planned to undergo either primary RYGB or SG will be recruited over a 2-year period from 2018 to 2019, and will be followed for up to 12 months postsurgery. Recruitment will take place at the Bariatric Centre for Weight Management and Metabolic Surgery, University College London Hospitals (UCLH) (study site) and the Bariatric and Obesity Surgery Clinic at the Whittington Hospital that acts as a participant identification centre (PIC). Participants recruited from the Whittington Hospital will have their surgical procedure undertaken at the same centre, but all study procedures such as written informed consent, baseline assessment, postsurgery follow-up care and study assessments will be undertaken by the bariatric team at UCLH. In both centres, the decision for procedure selection is based on informed patient preference after standardised counselling including details, potential risks, and benefits of each procedure that adheres to the current international guideline for the surgical recommendation for obesity and weight-related disease.^41^ This study is carried out by the Centre for Obesity Research, Division of Medicine, University College London (UCL), with an expected total duration of 36 months, from the first participant enrolled to last participant follow-up.

**Figure 1 F1:**
[figure not shown]
Flow diagram of participant enrolment, consent, assessment and associated timeline.

### Participants and recruitment

Patients will be screened for suitability for the study by the bariatric team at the study site and PIC based on the inclusion and exclusion criteria when they attend the standard presurgical assessment (box 1). Verbal consent will be sought from those fulfilling the eligibility criteria and interested in participating to be approached by a research investigator. Patients will be given a participant information sheet inviting them to participate in a 1-year prospective, longitudinal cohort study looking at the effect of bariatric surgery on body weight, body composition, PA levels, sedentary behaviour, physical function and strength, dietary intake, HRQoL, remission of comorbidities, healthcare resource utilisation and costs. Consented participants will then be scheduled to attend a baseline assessment, approximately 6 weeks before surgery day at the study site. Each participant will be given a Fitbit Alta HR to enable them to self-monitor their activity levels and to reduce sedentary behaviour. Based on the weekly number of bariatric procedures undertaken at UCLH and Whittington Hospital and after considering the eligibility criteria, estimated recruitment rate is approximately seven participants per month. Hence, the expected recruitment period for the study is 15–20 months.Box 1Participant eligibility criteria for participation in the BARI-LIFESTYLE observational studyInclusion criteriaAdult aged between 18 and 65 years.Planned to undergo either primary RYGB or SG surgery and fulfilling NICE eligibility criteria for bariatric surgery.^1^Able to read and write in English.Willing and able to provide written informed consent.Able to comply with study protocol.Willing and able to wear a Fitbit wrist-based activity tracker device and an ActiGraph device.Exclusion criteriaMore than 200 kg of body weight due to the limitation of DXA scan.Non-ambulatory.Functional limitation.DXA, dual-energy X-ray absorptiometry; NICE, National Institute for Health and Care Excellence; RYGB, Roux-en-Y gastric bypass; SG, sleeve gastrectomy.

All participants will receive the standardised postbariatric care as stipulated by NICE.^1^ Participants will attend the study site for monitoring of nutritional intake, vitamin and mineral deficiencies, comorbidities and medication review. Participants will receive verbal PA and dietary advice from a specialist nurse and dietitian at weeks 12 and 36 postsurgery, respectively.

### Outcomes measures

Outcome measures will be collected at four study time points, designed to coincide with normal follow-up care visits; baseline visit at approximately 6 weeks before surgery (T0) then at 3 (T1), 6 (T2) and 12 months (T3) postsurgery (table 1).

**Table 1 T1:** Study timeline and investigations

	Baseline (T0)	Day of surgery	3 months postsurgery (T1)	6 months postsurgery (T2)	12 months postsurgery (T3)
Sociodemographic data	✓				
Height	✓				
Weight	✓	✓	✓	✓	✓
Blood pressure and heart rate	✓		✓	✓	✓
Dual-energy X-ray absorptiometry scan	✓				✓
Bioelectrical impedance analysis	✓		✓	✓	✓
Laboratory test	✓		✓	✓	✓
Physical activity levels (ActiGraph) and activity diary	✓		✓	✓	✓
Physical function and strength					
6 min walk test	✓		✓	✓	✓
Sit-to-stand	✓		✓	✓	✓
Handgrip test	✓		✓	✓	✓
Dietary intake (3-day food diary)	✓		✓	✓	✓
Completion of questionnaires					
EuroQol-5D-3L	✓		✓	✓	✓
Impact of weight on Quality of Life-Lite	✓		✓	✓	✓
Beck Depression Inventory-II	✓		✓	✓	✓
Client Service Receipt Inventory	✓		✓	✓	✓
Review of medication	✓		✓	✓	✓
Review of comorbidities	✓		✓	✓	✓

#### Sociodemographic, medical history and physical examination

Participants’ sociodemographic data, medical history and physical examination will be completed by the bariatric team at the baseline visit. Data to be captured including age, gender, ethnicity, educational level, marital status, medication intake, weight history, pregnancy history, alcohol consumption using the Alcohol Use Disorders Identification Test-C (AUDIT-C) questions,^42^ smoking habits and family history of obesity and comorbidities.

### Primary outcome

Body weight will be measured using a weighing scale (Model VT200/220; Vishay Transducers, California, USA) with participants wearing light clothes and without shoes and heavy accessories, to the nearest 0.1 kg. Similarly, height will be determined using a stadiometer (Seca 242, Seca, Hamburg, Germany) to the nearest 0.01 m. %WL will be calculated using the following formula: %WL = ((weight on the day of surgery−weight at time point after surgery)/weight on the day of surgery)×100, measured at each study time point.

### Secondary outcomes

#### Body composition (body FM, LMM and BMD)

Body composition will be assessed at baseline and 12 months postsurgery using DXA scan (Discovery A DXA system, software V.13.4.2; Hologic; Massachusetts, USA). DXA scan uses ionising radiation to measure different body compartments. This is the current reference standard for assessing body composition and a gold standard method to diagnose osteopenia and osteoporosis.^43^ In addition, body composition will be measured using BIA (Tanita DC-430MAS; Tanita, Tokyo, Japan) at each study visit. This is a non-invasive, easy to perform and cheaper option to measure body composition that is based on the differences in electrical conductivity of FM and FFM tissues.^44^

#### PA levels and sedentary behaviour

PA and time spent in light, moderate and vigorous activities, and sedentary behaviour will be measured objectively using ActiGraph wGT3X-BT (Pensacola, Florida, USA), an accelerometer-based activity monitor.^45^ Participants will be instructed to wear the ActiGraph on their dominant hip for 1 week, from waking in the morning until going to bed at night, and to remove it only during water-based activities. Additionally, participants will be asked to keep an activity diary throughout the week, to assist interpretation of data from the device. Both the device and activity diary have to be returned to the investigators for data analysis (ActiLife software V.6.13.3; Pensacola, Florida, USA).

#### Physical function and strength

Participants’ functional capacity will be assessed using a 6MWT, a self-paced, submaximal assessment of functional capacity used to prescribe appropriate exercise.^46^ Lower body functional capacity and strength will be assessed using the STS test.^47^ Static muscle strength will be assessed using Jamar Hydraulic Hand Dynamometer (Patterson Medical; Illinois, USA).^48^

#### Dietary intake

All participants will be required to keep a 3 days food diary (two working days and one weekend day) for 1 week at each study time point. This method has a higher agreement with the 9 days food dairy compared with the food frequency questionnaire^49^while reducing the burden to patients and thus promoting better compliance for documenting food intake. The completed food diary will be returned to the investigators together with the ActiGraph and activity diary by using a stamped addressed envelope provided to participants.

#### Health-related quality of life

HRQoL will be assessed using EQ-5D-3L and IWQOL-Lite. The EQ-5D-3L descriptive system is a 5-item self-report questionnaire that assesses the following domains: mobility, self-care, usual activities, pain/discomfort and anxiety/depression, and a visual analogue scale, which records self-rated health on a 0–100 scale.^50^ EQ-5D-3L health states will be converted into utility values using a formula that attaches weights to each level in each dimension based on valuations by general population samples. We will use a value set for the UK population to calculate utility values at each time point for every participant.^51^ The IWQOL-Lite is a 31-item, self-report, obesity and overweight-specific measure of HRQoL.^52^ This tool consists of a total score and scores on each of five scales – physical function, self-esteem, sexual life, public distress, and work; higher scores indicate better HRQoL.

#### Attitude and symptoms of depression

BDI-II is a 21-item self-report questionnaire that assesses mood over the past week.^53^ Symptoms of depression are classified by the total score: minimal, mild, moderate, and severe symptoms.

#### Obesity-associated comorbidities

Comorbidities (T2D, dyslipidaemia, hypertension, OSA) and medication review will be carried out at each study time point.

#### Healthcare resource utilisation and costs

Resource use data will be collected using an adapted version of the CSRI,^54^ including the costs of bariatric surgery plus presurgery visits, number of contacts with healthcare professionals, visits to specialist clinics, the emergency department, admissions to the hospital, primary care contacts, and medications. Resource use data will be converted into costs using published unit costs.^55–57^ In addition, information regarding support from informal carers, employment status and time off work will be collected. Resource use data will be collected for the previous 6 months at the baseline visit and since participants’ last study visit at each postsurgery study time point.

### Sample size

A sample size of 100 patients will be enough to model the primary outcome and the range of secondary outcomes with a reasonable level precision and with regard to the number of patients who are likely to be recruited within the study’s time frame. Also, a sample size of 100 patients will be sufficient to estimate the %WL at 1 year postsurgery to within ±2.5% using a 95% CI. This calculation accounts for a possible drop-out rate of up to 25% and assumes a conservative estimate for SD of %WL of 10%. This sample size should also ensure that there are enough data points for linear mixed effects models to be fitted with parameter estimates that have a satisfactory level of precision and where the model fitting algorithm will converge.

### Statistical analysis

The demographic and medical history information collected at baseline shall be presented in a table. Categorical variables shall be reported as raw numbers and percentages. Reports of continuous variables shall include mean, median, range and SD.

#### Primary outcome analysis

The primary outcome is the %WL measured longitudinally at baseline and 12 months postsurgery. %WL will be analysed using a linear mixed effects model over the three postsurgery time points (3 months, 6 months and 12 months) after controlling for the baseline body weight measure and height. Model assumptions shall be checked and suitable transforms of the primary outcome variable considered if necessary. In addition, overall percentage change in weight since baseline shall be computed marginally at each of 3, 6 and 12 months and displayed graphically.

#### Secondary outcomes analyses

Analyses of longitudinal secondary outcomes shall be performed using linear mixed effects regression models, with a normal distribution assumed for continuous outcomes (or a suitable transform of these outcomes). Model parameter estimates together with appropriate 95% CIs shall be reported. Categorical outcomes (eg, proportions of participants with comorbidities) shall be summarised in tabular form at each time point. Where appropriate (for example, for proportions), estimates and 95% CIs will be presented. To analyse costs, we will assume the costs measured at baseline for the preceding 6 months would persist during follow-up in the absence of surgery; we will then compare postsurgery costs with predicted costs that would have been incurred in the absence of surgery. To account for skewness of the cost data, we will use a generalised linear model with gamma family and log link.^58^

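### The six months of cost carried forward as the no-surgery cost fall in the run-up to surgery, and no exclusion of presurgical work-up is stated; other things equal, this overstates the saving

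*Protocol article*

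**What the plan says.** The protocol article, under Secondary outcomes analyses, sets the comparator for costs: "we will assume the costs measured at baseline for the preceding 6 months would persist during follow-up in the absence of surgery". The analysis will then "compare postsurgery costs with predicted costs that would have been incurred in the absence of surgery", using a gamma generalised linear model with log link to handle skewness.

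The section Healthcare resource utilisation and costs fixes the window: "Resource use data will be collected for the previous 6 months at the baseline visit". At later visits the recall runs from the previous study visit. The adapted Client Service Receipt Inventory (CSRI) covers resource use "including the costs of bariatric surgery plus presurgery visits, number of contacts with healthcare professionals, visits to specialist clinics", followed by emergency visits, admissions, primary care and medications.

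On timing, Participants and recruitment says that patients are screened "when they attend the standard presurgical assessment". They then consent and are booked for baseline. Outcomes measures puts baseline (T0) about 6 weeks before surgery and the last visit (T3) at 12 months after it. All participants are already planned for one of the two operations. Advantage and limitation states that there is no non-surgical comparator group.

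**The concern.** The comparator is meant to be what care would have cost had surgery not taken place. It is built from a period in which every participant was heading for surgery. Contacts that exist only because an operation is planned would not recur in a world without it, yet the rule projects the whole baseline cost, and neither cost passage removes them.

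Costs are a named objective, and the Introduction raises the question of whether savings offset the initial cost of surgery. With no non-surgical group, nothing else in the design can correct the comparator. The gamma model deals with the shape of the cost distribution, not with what the baseline cost contains. If the work-up share is material, an apparent saving could shrink, vanish or reverse.

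**Working it through.** The article states no cost figure, so there is none to reproduce. The check is of the rule itself.

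**Inputs**
- Projection rule: baseline 6-month cost persists during follow-up (Secondary outcomes analyses).
- Recall: 6 months before T0, then since the last study visit (Healthcare resource utilisation and costs).
- T0 about 6 weeks, or 1.5 months, before surgery; last visit at 12 months (Outcomes measures).
- Work-up share s of baseline cost: not in the document. Assumed values of 10%, 25% and 40% show the range.

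**1. Where the window lies.** It ends about 1.5 months before surgery and starts about 1.5 + 6 = 7.5 months before it. The presurgical assessment used for screening precedes T0; the interval between them is not given.

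**2. Effect on the prediction.** Let the baseline 6-month cost be B + W, with B background care and W work-up.
- Planned 12-month prediction: (12/6) × (B + W) = 2B + 2W.
- Prediction without work-up: 2B.
- Excess: 2W. Relative excess: 2W/2B = W/B = s/(1-s), where s = W/(B + W).

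**3. Numbers, with B + W indexed at 100.** The planned prediction is 200. The last two columns take a hypothetical observed 12-month cost of 150.

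| s | Prediction without work-up | Excess 2W | Relative excess | Saving as planned | Saving without work-up |
|---|---|---|---|---|---|
| 10% | 180 | 20 | 11% | 50 | 30 |
| 25% | 150 | 50 | 33% | 50 | 0 |
| 40% | 120 | 80 | 67% | 50 | -30 |

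**4. Does booking presurgery visits to surgery cure it?** Let C be all other surgical and postsurgical cost. The coherent contrast is 2B - (C + W).
- W in the baseline and also booked to surgery: 2(B + W) - (C + W). The saving is too high by 2W.
- W in the baseline only: 2(B + W) - C. Too high by 3W.
- W removed from the baseline and booked to surgery: no bias.

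Only removal from the baseline cures it.

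**5. What acts the other way.**
- *Background trend.* If background cost without surgery rose by a fraction g, the bias would cancel when 2Bg = 2W, so g = s/(1-s): 11% at s=10%, 33% at s=25%.
- *The 3-month (T1) recall.* It starts at T0, so it takes in about 1.5 months before surgery. If observed use over 13.5 months is set against a 12-month prediction, the observed side carries extra background cost of 1.5 × B/6 = 0.25B. On the index this is 22.5 against 2W = 20 at s=10%, 18.75 against 50 at s=25%, and 15 against 80 at s=40%. The two cancel when W/B = 0.125, that is s = 0.125/1.125 = 11%. Work-up in those weeks is properly a cost of surgery and is not counted here.
- If both sides cover 13.5 months, this second offset disappears and the excess becomes (13.5/6)W = 2.25W.

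**The case against.** The strongest reply is that the article pairs presurgery visits with the operation as one cost item ("including the costs of bariatric surgery plus presurgery visits") and lists other contacts after it. That may well mean they are costed as part of surgery. The reading is plausible, but it settles only the surgery side. The projection uses the costs measured at baseline without exception, and booking the visits to surgery as well still leaves 2W in the comparator.

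A second reply is that a journal article condenses, and item-level allocation may sit in a fuller document. That could explain a missing detail. Here, however, the rule is stated, and followed as written it projects surgery-induced contacts into the no-surgery scenario. If the exclusion is already intended, one sentence would close the point.

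Two stronger readings are tempting and are not supported. A reader might infer that the comparison is always biased in favour of surgery. The direction is clear only for this component: background trend and the T1 recall can act the other way and, at a small share, could cancel it. A reader might also infer that the rule alone dictates the cost conclusion. Postsurgery costs are observed, the work-up share is unknown, and if it is small the result hardly moves. Nor does the document say that every presurgical contact would stop without surgery, or whether work-up is double counted with the surgical cost or omitted from it.

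It is also fair to say that the rule is openly labelled an assumption and the lack of a comparator is disclosed.

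**Conclusion.** The point stands as a weakness in a stated rule for a secondary outcome. The baseline window lies in the run-up to planned surgery, the costed items include presurgery visits and specialist clinics, and no exclusion is stated before the cost is carried forward. Other things equal, the predicted 12-month no-surgery cost is too high by 2W, or s/(1-s) in relative terms, and the saving is overstated by at least 2W.

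This rests on three assumptions: work-up contacts fall inside the 6-month window, they would not occur without planned surgery, and they are not removed before projection. The size cannot be computed from the document, so the percentages are illustrations. The net direction of the whole comparison is not established, because of the two offsets above. The primary outcome, percentage weight loss, is untouched.

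**What to change.** In the cost analysis:
1. Flag bariatric-pathway contacts in the baseline CSRI and in the part of the T1 recall that runs from T0 to the day of surgery.
2. Exclude them from the cost carried forward.
3. Count them once, as cost of surgery.
4. Make the observed and predicted periods the same length, either 12 months from surgery or about 13.5 months from T0, and say which.
5. Report the all-inclusive carry-forward as a sensitivity analysis. Varying the background cost trend alongside it would show how far the conclusion depends on the persistence assumption.

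The cost is a few sentences in the analysis plan and some recoding of collected data. If the CSRI does not separate pathway contacts or date them around surgery, clinic records or an added item will be needed. The reported saving may become less favourable. No change to recruitment, visits or sample size follows.

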#### Missing data

Bias due to missing data will be investigated by comparing the baseline characteristics of participants with and without missing values. Depending on the extent of missingness, the predictors of missing values will be identified. The primary outcome analysis will be adjusted for those predictors of missing values, which are related to missingness. Multiple imputation using chained equations shall be considered as part of a sensitivity analysis for missing data in the primary outcome model.

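### The one sensitivity method named for missing %WL, chained-equation imputation, would largely repeat the mixed model and could not show bias if poor responders miss the 12-month visit

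*Protocol article*

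**What the plan says.** The Primary outcome analysis section of the protocol article sets the main model: "WL will be analysed using a linear mixed effects model over the three postsurgery time points (3 months, 6 months and 12 months". The only covariates that it lists are weight at baseline and height.

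The Missing data section adds three steps:

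- **A descriptive check.** "Bias due to missing data will be investigated by comparing the baseline characteristics of participants with and without missing values".
- **A possible change to the primary model.** If enough data are missing, predictors of missingness are looked for, and then "The primary outcome analysis will be adjusted for those predictors of missing values, which are related to missingness". The article gives no threshold, candidate list or selection rule.
- **A sensitivity analysis.** "Multiple imputation using chained equations shall be considered as part of a sensitivity analysis for missing data in the primary outcome model". No other method is named, and the assumption behind this one is not stated.

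The Sample size section allows for loss only as a matter of precision: "This calculation accounts for a possible drop-out rate of up to 25% and assumes a conservative estimate for SD of %WL of 10" percentage points.

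**The concern.** A likelihood-based mixed model and standard chained-equation imputation both treat the missing values as predictable from what was observed. If the two use much the same variables, they should agree whether that assumption is true or false, so their agreement is weak evidence that it is true.

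The obvious threat in this cohort is that patients whose weight loss has stalled do not attend at 12 months, for reasons that their earlier weights do not reveal. Mean %WL at one year would then be too high. A comparison of baseline characteristics cannot see this, because the loss depends on a weight that was never measured. The 95% CI reflects sampling error only, and a reader shown close agreement between model and imputation would be reassured without cause.

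A smaller matter goes with it. The covariates of the primary model may change with what the missing-data pattern shows, so two analysts with the same data could report different primary estimates.

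**Working it through.** **1. The plan's own precision figure.** Inputs from the Sample size section: N = 100, drop-out up to 25%, SD 10 points, target half-width 2.5.

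- Completers: 100 × (1 − 0.25) = 75.
- Standard error: 10/√75 = 1.155.
- Half-width: 1.96 × 1.155 = 2.26 (normal) or 2.30 (t, 74 df).

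The claim that 100 patients suffice for ±2.5 is correct. The half-width of about 2.3 is the yardstick for bias.

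**2. Does same-variable imputation reveal loss that is not at random?** This was checked by simulation. The documents give none of the following inputs except N and the 12-month SD, so the rest are assumptions:

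- mean %WL of 17, 24 and 28 at 3, 6 and 12 months, with SDs 6, 8 and 10;
- correlations 0.85 (3 with 6 months), 0.70 (3 with 12) and 0.85 (6 with 12);
- 3- and 6-month values complete, and about 26% missing at 12 months, more often in patients with low %WL;
- no covariates; 100 patients per data set; 4,000 data sets, with imputation (20 draws) in 800 of them.

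The likelihood estimate was obtained by regressing the 12-month value on the 3- and 6-month values, which is what an unstructured mixed model does with this pattern. Imputation used the same variables.

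| Drop-out depends on | Bias, completers only | Bias, mixed model | Bias, imputation | Mean absolute difference, imputation vs model |
|---|---|---|---|---|
| 6-month value (at random) | 2.09 | −0.01 | 0.00 | 0.06 |
| 12-month value (not at random) | 2.52 | 0.81 | 0.80 | 0.06 |

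Two things follow. The mixed model removes essentially all of the bias in the first row and about two thirds in the second ((2.52 − 0.81)/2.52 = 68%). And the gap between imputation and model is the same in both rows, so it does not tell them apart.

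**3. Size of what remains.** Let f be the fraction missing at 12 months and δ the average shortfall of the missing patients below what the model predicts for them. Then bias in the mean = f × δ. The documents give no δ, so a range is shown. Coverage is approximate, with SE = 10/√(100(1 − f)), and equals Φ(1.96 − bias/SE) − Φ(−1.96 − bias/SE).

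| f | δ (assumed) | Bias | Coverage of nominal 95% CI |
|---|---|---|---|
| 0.25 | 2 | 0.50 | 92.8% |
| 0.25 | 5 | 1.25 | 80.9% |
| 0.25 | 10 (extreme) | 2.50 | 42% |
| 0.10 | 5 | 0.50 | 92.4% |

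For orientation, the 0.81-point bias in step 2 corresponds to δ = 0.81/0.258 = 3.1, inside the 2 to 5 range. With SE 1.155 it would bring coverage to about 89%.

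**The case against.** Several points on the other side stand.

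- **Only a condensed article is shown.** An analysis for data missing not at random is commonly left to the SAP or the full protocol, so its absence here is not in itself a fault. The point rests on the method that the article does name and on what that method can show.
- **A reader might infer that this is the only sensitivity analysis planned.** The text does not say so. Imputation is to be considered as one part of a sensitivity analysis, which neither commits to it nor rules out others.
- **A reader might infer that imputation tests nothing.** The article does not restrict the imputation model to the variables in the mixed model. Table 1 lists impedance, laboratory tests, questionnaires and comorbidity review at 3 and 6 months, and imputation that used them would condition on more than the mixed model does. The near-identity in step 2 holds for the same variables. Even richer imputation would still assume missing at random.
- **A reader might infer that up to a quarter of the cohort is informatively lost and untested.** The 25% is a planning ceiling for precision, and nothing calls it informative. Loss predictable from baseline or from earlier weights is handled by the longitudinal model and the planned adjustment.
- **A bias as large as the whole ±2.5 is not a fair headline.** It needs every missing patient to fall, on average, a full marginal SD below prediction at the maximum drop-out.
- **Choosing covariates by their relation to missingness is a recognised way to make missing at random more plausible.** The Advantage and limitation section says that the study does not aim to compare the two procedures, so no between-group error rate is inflated. The cost is a primary estimate that is not fully fixed in advance. Simply removing those covariates would have a cost of its own.

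None of this gives the named check the power to reveal loss that depends on the unseen 12-month weight.

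**Conclusion.** The point holds as an inexpensive improvement to the stated method, not as an error that invalidates the plan. Standard chained-equation imputation shares the mixed model's assumption; with the same variables the two differed by about 0.06 points on average whether or not that assumption was true. Neither imputation nor the baseline comparison can show bias from poor responders missing the 12-month visit.

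At the 25% ceiling the residual bias would be about 0.5 to 1.25 points for assumed shortfalls of 2 to 5 points below prediction, roughly a fifth to just over a half of the 2.3-point half-width. It is proportionately smaller with less loss. These sizes rest on assumed shortfalls and, for the simulation, on assumed correlations and complete 3- and 6-month data. The sample-size statement is sound.

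**What to change.** 1. Commit to the sensitivity analysis instead of leaving it to be considered.
2. Extend it to delta-adjusted multiple imputation: lower the imputed 12-month %WL by a stated range, for example 0, 2.5 and 5 points, with larger values labelled as extreme, and report the mean and 95% CI at each. At 25% missing these shifts move the mean by 0, 0.625 and 1.25 points, so readers can judge how large a shortfall would change the message.
3. Put the predictors of missingness and the 3- and 6-month measures into the imputation model as auxiliary variables.
4. Report the primary estimate with baseline weight and height alone beside any version that is also adjusted for predictors found in the data. This keeps one estimate fixed in advance without giving up the adjustment. No other covariate needs to be added for this purpose.

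If the SAP already contains such an analysis, a sentence in the article pointing to it would be enough for items 1 and 2. The cost is slightly more analysis on data already collected, and a range of results in place of a single figure.
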